
### Inclusion criteria

Histologically proven initial diagnosis of adenocarcinoma of the prostate.Biochemical relapse of PCa following radical local prostate treatment (RP, primary RT or RP +/− prostate bed [PB] adjuvant/salvage RT) according to the EAU guidelines 2019 [1].Following RP, patients with a biochemical relapse are eligible in case a nodal relapse is detected in the pelvis even in the absence of prior postoperative PB radiotherapy (adjuvant or salvage).In case of a suspected local recurrence following primary RT, a biopsy should confirm local recurrence. Patients with a confirmed local recurrence are eligible in case they also undergo a local salvage therapy.Nodal relapse in the pelvis on choline, PSMA or FACBC PET-CT or PET-MRI with a maximum of 5 positive nodal lymph nodes. The upper limit of the pelvis is defined as the aortic bifurcation.WHO performance state 0–1Age ≥ 18 yearsAbsence of any psychological, familial, sociological or geographical condition potentially hampering compliance with the study protocol and follow-up schedule; those conditions should be discussed with the patient before registration in the trial.Before patient registration/randomization, written informed consent must be given according to ICH/GCP and national/local regulations.

### Exclusion criteria

Bone or visceral metastasesPara-aortic lymph node metastases (above the aortic bifurcation)Local relapse in the prostate gland or bed not suitable for curative treatmentPrevious irradiation of the pelvic and/or para-aortic nodesSerum testosterone level < 50 ng/dL or 1.7 nmol/L at time of randomizationSymptomatic metastasesLymph node metastases in previously irradiated areas resulting in dose constraint violationContraindications to pelvic radiotherapy (e.g. chronic pelvic inflammatory bowel disease)Contraindications to ADTPSA rise while on active treatment with ADT (LHRH-agonist, LHRH-antagonist, anti-androgen, estrogen)Previous treatment with a cytotoxic agent for PCaTreatment during the past month with products known to influence PSA levels (e.g. fluconazole, finasteride, corticosteroids …)Other active malignancy, except non-melanoma skin cancer or other malignancies with a documented disease-free survival for a minimum of 3 years before randomization.Patients can only be randomized in this trial once.

### Pre-randomization and evaluation

Patients must be restaged within 8 weeks prior to randomization with either a whole-body choline, PSMA or FACBC PET-CT/−MRI to exclude M1 disease (para-aortic node(s), bone or visceral metastases). Additional imaging modalities to confirm or to rule out M1 disease are optional. For patients without prior RP it is recommended to perform a multiparametric MRI of the prostate to rule out local recurrence. Local relapses must be biopsy proven. The following pre-treatment work-up, which is also depicted in Table 1, must be performed:

**Table 1 Tab1:** Summary of study visits and procedures

TIMEPOINT				STUDY PERIOD						
	Screening		Allocation	Treatment period			Follow-up period			
	Within 8 weeks prior to randomization	Within 2 weeks prior to randomization	Baseline	Start	During	End	1 month after treatment ± 7 days	3 months after treatment ± 14 days	6 months after treatment ± 14 days	6-monthly, yearly, until progression (g) ± 14 days
Window										
**ENROLMENT:**										
**Eligibility screen**	x									
**Signed ICF**	x									
**Randomization**			x							
**INTERVENTIONS (a,b):**										
**If sLND**				x	x	x				
**If WPRT**				x	x	x				
**If SBRT**				x	x	x				
**ADT**				x	x	x	x	x	x	
**ASSESSMENTS:**										
**Medical history**	x									
**Patients characteristics**		x								
**Physical exam (c)**		x				x	x	x	x	x
**Lab**										
PSA		x				x (h)	x	x	x	x
Testosterone		x					x	x	x	x
Biomarker		x								x (i)
**Imaging**										
PET-CT (d)	x							(x)	(x)	(x)
MRI (e)	x									
**Adverse Events**										
Baseline toxicity		x								
Acute toxicity (f)				(x)	(x)	x	x	x		
Late toxicity									x	x
**Medication**										
Prior medication		x								
Con med’s						x	x	x	x	x
**Quality of life**										
QLQ-C30		x						x	x	x
QLQ-PR25		x						x	x	x
**Survival status**							x	x	x	x

(a) All arms should receive an LHRH-agonist or antagonist for a duration of 6 months using 1 monthly formulations. In case of SBRT/WPRT, ADT should start no later than the first fraction (whichever RT treatment comes first) and no earlier than 2 weeks before the start of radiotherapy. In case of sLND, ADT should be started no earlier than 1 day postoperatively and no later than 10 days postoperatively

(b) Treatment should start preferably within 4 weeks after randomization, but no later than 8 weeks after randomization. Treatment period is defined as the time between first treatment day and last treatment of surgery and/or radiotherapy

(c) Physical examination including scoring of Performance Status. Weight and height will only be measured at screening

(d) Whole body choline, PSMA or FACBC PET-CT/−MRI. During follow-up repeat PET-CT only at time of biochemical relapse and then 6-monthly afterwards until clinical progression is determined or earlier in case of symptomatic progression

(e) Optional: for patients without a prior radical prostatectomy it is recommended to perform a multiparametric MRI of the prostate to rule out local recurrence

(f) During the treatment period a toxicity assessment should be done at least once a week in case of WPRT. For SBRT toxicity assessment should be done only at end of treatment, for sLND at discharge (Clavien-Dindo scale)

(g) 6-monthly follow-up for a minimum of 24 months, with yearly follow-up thereafter up to 60 months or until progression. In case of clinical progression, the patient will be treated according to the EAU guidelines

(h) In case of SBRT/WPRT, PSA has to be determined on the day of the last fraction. In case of sLND in arm A, PSA will be determined at 4 weeks after surgery (follow-up month 1). In case of sLND + WPRT in arm B, PSA will be determined at 4 weeks post-WPRT (follow-up month 1)

(i) At time of primary endpoint is reached, a new biomarker sampling is preferred, but optional

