#### Secondary endpoints

Clinical PFS: time between randomization and the appearance of a new recurrence (any N1 or M1) as suggested by PET-CT or PET-MRI, symptoms related to progressive PCa or death due to any cause.Local recurrence: evidence of a recurrence on imaging inside the surgical or radiotherapy field. Confirmation per biopsy is recommended. For radiotherapy schedules, local response and local progression is defined as per RECIST 1.1 criteria.Regional nodal recurrence: radiographic evidence (PET-CT or -MRI) of lymphadenopathy in the pelvis, outside the surgical or radiotherapy field. Histologic confirmation is recommended, especially in the absence of biochemical recurrence.Distant recurrence: appearance of distant metastases (M1a, M1b, M1c) outside the pelvis evidenced by PET-CT or -MRI.Biochemical PFS: time between randomization and the day of the first recorded biochemical progression (as defined below), clinical progression or death due to clinical progression.RP at diagnosis: biochemical recurrence = PSA > 0.20 ng/mL, confirmed 2 weeks later.Prostate radiotherapy at diagnosis: biochemical recurrence = PSA nadir + 2 ng/mL (Phoenix definition).Patients whose PSA does not drop below 0.20 ng/mL (if previous RP) or below the level before treatment (if previous prostate radiotherapy) at time of first response assessment at 3 months follow-up, are considered as non-responders to treatment and are considered to have a biochemical recurrence in case a second measurement at least 2 weeks later confirms a stable or rising PSA above this level.Time to start of hormonal treatment: time from trial randomization to start of hormonal treatment.Time to castration-resistant disease: time from trial randomization until castration resistant status as defined in the EAU-guidelines [1].PCa-specific survival: time from trial randomization until death due to PCa.Overall survival (OS): time from trial randomization until death from any cause.Acute and late toxicity due to radiotherapy will be assessed according to the National Cancer Institute Common Terminology Criteria for Adverse Events (CTCAE) version 4.0 [20], with special attention for rectal, gastro-intestinal and urinary adverse events. Surgery related morbidity, e.g. intra-operative complications (blood loss, injury to other pelvic organs …), and post-operative surgical complications will be scored using the Clavien-Dindo Classification of Surgical Complications [21].Acute toxicity: occurring during and up to 3 months after treatment completion.Late toxicity: occurring later than 3 months after treatment completion.Quality of life (QoL) scoring using the EORTC QLQ-C30 supplemented with QLQ-PR25. Raw scores will be transformed to a linear scale ranging from 0 to 100 according to the EORTC manual. The multi-item scales of the QLQ PR-25 will be analysed at both the individual item and the scale level. The results will be presented in accordance with recent guidelines for reporting health related QoL randomized controlled trials [22].Pattern of progression.Sensitivity/specificity of PET-imaging for the detection of nodal recurrences: limited to patients undergoing surgery.Biomarker discovery: to develop a miRNA panel predictive for treatment response using whole genome miRNA expression profiling [23].

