### Follow-up

Follow-up is planned at month 1, 3 and 6 following treatment completion, 6-monthly thereafter until month 24 and then yearly up to month 60. Patients who withdraw from trial treatment in the absence of progression should continue to have follow-up visits as defined above. The following investigations should be performed at every follow-up visit (Table 1):
Clinical examination with late toxicity scoringPSA and testosterone measurementQoL-scoringPET-imaging only at time of biochemical progression or symptomatic progression and then 6-monthly thereafter until clinical progression is determined. In case of biochemical progression, the PSA should at least be 0.50 ng/mL before a new PET-CT scan should be considered. The location of progression should be recorded.At time of primary endpoint is reached, a new biomarker sampling is preferred, but optional.Concomitant medicationSurvival status

In case of clinical disease progression the patient will be treated according to each centre policy, but adherence to the EAU guidelines [24] is recommended. In case of local or regional oligometastatic recurrence during follow-up, a new MDT is allowed (this treatment falls outside the scope of this protocol).

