#### Androgen deprivation therapy

All arms should receive an LHRH-agonist or -antagonist for a duration of 6 months using 1-monthly formulations. In case of LHRH-agonist, flare prevention with an anti-androgen is recommended for at least 5 days prior to the first injection of the agonist and should not be continued for longer than 15 days of the first month duration. ADT-related toxicity should be managed according to Nguyen et al. [34].
In case of sLND, ADT should be started between day 1 and day 10 postoperatively.In case of SBRT/WPRT, ADT should start no later than the first day of WPRT and no earlier than 1 week before the start of SBRT/WPRT.

Palliative ADT should not be started for biochemical progression without documented clinical progression. In case of symptomatic progression, palliative ADT is mandatory. In case of clinical asymptomatic progression, delayed ADT until progression to a symptomatic state is allowed in well informed men (EAU 2019 guidelines). In general, starting ADT in asymptomatic patients is recommended only if conventional imaging confirms clinical progression. The start of ADT for PET-positive lesions not suspicious on conventional imaging (CT/MRI/bone scintigraphy) is not recommended. In case of clinical oligometastatic progression, repetition of MDT is allowed for all arms.

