### Statistical analysis

#### Sample size

This prospective randomized phase II design aims to determine whether the treatment arm can be tested in a subsequent phase III trial. Patients will be randomized (1:1) to receive either arm A: MDT (sLND or SBRT) plus ADT or arm B: WPRT plus MDT (focal radiotherapy boost or sLND) plus ADT. Stratification is according to the type of MDT and the type of PET-tracer. The sample size is based on the stratified Log-rank test. A scenario analysis has been performed to reflect the different and reasonable possible values of the parameters. The two-sided significance level alpha was set at 0.20 and the power maintained at 80%. In this chosen scenario, the median MFS following MDT has been estimated as 24 months in arm A. Assuming uniform accrual over 48 months with 24 months additional follow-up time, a total of 178 patients are needed to detect a 12-month difference in median MFS from 24 to 36 months, considering a 5% rate of loss to follow-up. The total study length will be 72 months.

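### Table 1 ends follow-up visits at progression while the Follow-up section runs them to month 60; under Table 1, CRPC and prostate-cancer death would go mostly unobserved and OS would be informatively censored

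*Protocol article*

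**What the plan says.** The protocol article gives the visit schedule in two places, and they differ.

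- **Table 1.** The header of the last follow-up column reads "6-monthly, yearly, until progression (g", where the letter points to a table note. Note (g) reads "6-monthly follow-up for a minimum of 24 months, with yearly follow-up thereafter up to 60 months or until progression". Survival status, testosterone, late toxicity, concomitant medication and both QoL questionnaires are all scheduled in that column.
- **Follow-up section.** After the month 6 visit, visits run "6-monthly thereafter until month 24 and then yearly up to month 60". The same items, survival status included, are listed for every visit, and no stop at progression is stated. The one sentence on continuation covers patients who leave trial treatment without having progressed.

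Two other sections determine what this conflict affects.

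- **Androgen deprivation therapy:** "Palliative ADT should not be started for biochemical progression without documented clinical progression". The section also lets well-informed men with asymptomatic clinical progression delay ADT until symptoms.
- **Secondary endpoints:** time to start of hormonal treatment, prostate-cancer-specific survival, overall survival, and castration resistance, defined as "time from trial randomization until castration resistant status as defined in the EAU-guidelines". All four run from randomization.

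**The concern.** Under the Table 1 schedule, a man's last visit falls at progression. By the protocol's own sequence, palliative ADT starts then or later, castration resistance generally comes after that, and prostate-cancer death comes last. Sites working from the table would stop looking just as these events become likely. Censoring at progression is also informative, because the men censored are those at highest risk of the event.

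The Background expects the experimental arm to postpone palliative systemic treatment while QoL is maintained. After relapse, that expectation would go largely untested. If WPRT delays progression, arm B would also be observed for longer than arm A, including for late toxicity.

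The point is confined to the visit rule and the secondary endpoints.

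**Working it through.** **1. Is the planned timeline coherent?** The Sample size section states "The two-sided significance level alpha was set at 0.20 and the power maintained at 80"%, and "a total of 178 patients are needed to detect a 12-month difference in median MFS from 24 to 36 months". It assumes 1:1 allocation, 48 months of uniform accrual, 24 further months of follow-up and 5% loss.

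- Events (Schoenfeld): 4 × (1.2816 + 0.8416)² / (ln 0.667)² = 110. Freedman's formula gives 113.
- Event probability with λ = ln 2 / median: 1 − (e^(−24λ) − e^(−72λ)) / (48λ). This is 0.7295 at a median of 24 months and 0.589 at 36 months, mean 0.659.
- N = 110 / 0.659 = 166.9, and 166.9 / 0.95 = 176. With 113 events, N = 181.

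Both are close to 178, so potential follow-up of 24 to 72 months per man can be used below. Nothing in this point changes N.

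**2. Follow-up time lost under a strict stop at progression.** Let potential follow-up F be uniform on 24–72 months and capped at the planned 60. Its mean is 0.75 × 42 + 0.25 × 60 = 46.5 months. Progression is assumed exponential, with the 12–18 month median that the Background quotes from earlier MDT series. Mean observed time is the integral from 0 to 60 of 2^(−t/median) × P(F > t). Here P(F > t) is 1 up to month 24 and (72 − t)/48 after it. Loss to follow-up is ignored, and the gap between randomization and end of treatment is neglected.

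| Median to progression | Progress within F | Observed (months) | Share of 46.5 |
|---|---|---|---|
| 12 | 91% | 15.8 | 34% |
| 18 | 81% | 21.1 | 45% |
| 24 (assumed) | 72% | 25.0 | 54% |
| 36 (assumed) | 58% | 30.1 | 65% |

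**3. The lenient reading of note (g).** Suppose the 24-month minimum applies to everyone and progression ends only the yearly phase. The share progressed by month 24 is 1 − 2^(−24/18) = 60% to 1 − 2^(−24/12) = 75%. These men have no visits from month 24 to month 60.

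**4. Imbalance between arms.** Assume progression medians of 15 and 22.5 months. The ratio 15/22.5 = 0.667 is borrowed from the effect planned for MFS.

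| Reading | 15 months | 22.5 months | Ratio |
|---|---|---|---|
| Strict stop, 60 months available to all: (median/ln 2) × (1 − 2^(−60/median)) | 20.3 | 27.3 | 1.35 |
| Strict stop, staggered follow-up as in step 2 | 18.7 | 24.2 | 1.29 |
| 24-month minimum for all, staggered follow-up | 28.2 | 31.2 | 1.11 |

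Under the Follow-up section's schedule, progression creates no such difference.

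**5. Overall survival.** The document gives no death rates. In a simulation with assumed 5-year other-cause mortality of 3–10% and assumed median prostate-cancer survival after progression of 36–84 months, about 2–15% of deaths precede progression when the progression median is 12–18 months. The range is 4–28% when that median is 24–36 months.

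**The case against.** The strongest reply is that the favourable schedule is already in the document. The Follow-up section runs visits and survival status to month 60. Note (g) can be read as 24 months of visits for everyone. It does not define progression, although note (d) suggests clinical progression. Note (i) expects a sample when the primary endpoint is reached, which suggests observation beyond a nodal-only relapse. A condensed article may also leave post-progression contact to the full protocol.

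Much of this stands. A reader might infer that the plan itself puts these endpoints outside the observed period. The documents do not support that: they contradict themselves, and only one side of the contradiction has this effect. Other strong readings also fail:

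- **That almost no palliative ADT start would be seen.** The protocol makes ADT mandatory at symptomatic progression, and a start at the progression visit can be recorded. Only delayed starts are lost.
- **That OS is almost wholly unobserved.** Deaths without progression are still captured.
- **That arm B gets 35% more observation.** This is the top of a range that starts near 11%.
- **That toxicity of salvage treatment is missed.** The late-toxicity endpoint is toxicity due to radiotherapy, and a new MDT after relapse is declared outside the protocol's scope.
- **That a particular toxicity analysis must be fixed here.** That choice can be left to the SAP.

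The reply does not remove the conflict. The column header gives no support to the 24-month reading, the Follow-up section's continuation sentence fits the Table 1 reading, and step 3 shows that the lenient reading still loses most men after month 24.

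**Conclusion.** The inconsistency is real and should be resolved. Three schedules can be read from one document: to month 60 regardless of progression, to progression, or to month 24 and then to progression. Sites may follow different ones.

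If Table 1 is followed, CRPC and prostate-cancer death would be mostly unobserved, delayed ADT starts would be missed, and OS would be informatively censored. A strict stop keeps about 34–45% of potential follow-up time. The lenient reading leaves 60–75% of men without visits after month 24. Observed time would differ between arms by a ratio of about 1.1 to 1.35.

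These sizes rest on exponential progression, on a median from earlier MDT series rather than from this regimen with its mandatory ADT, and on a borrowed hazard ratio. Longer medians shrink the loss, but at 36 months a strict stop would still discard about a third of the time.

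**What to change.** In the Table 1 header and note (g), remove progression as a stop for visits, so that both match the Follow-up section. In that section, state that survival status with cause of death, date of palliative ADT start, CRPC date, late radiotherapy toxicity and QoL are collected to month 60 or death, irrespective of progression. Reword its continuation sentence so that it is not limited to men without progression.

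The sample size of 178 is unchanged, and no treatment rule needs to change. The cost is continued visits and data entry for men who have progressed, which the Follow-up section already plans. The change should come before more men leave the schedule, because uncollected post-progression data may not be recoverable.

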#### Within 8 weeks prior to randomization

Signed ICFWhole-body choline, PSMA or FACBC PET-CT/PET-MRIMedical history (including previous therapies and PSA values)In- and exclusion criteria

#### Within 2 weeks prior to randomization

Patient characteristicsBaseline symptoms (including gastrointestinal and genitourinary morbidity) and medicationQoL questionnaires (QLQ-C30, QLQ-PR25)Physical examination including scoring of Performance Status, weight and heightBaseline pre-treatment PSA and testosterone determinationBiomarker collection

### Randomization

Treatment will be allocated at random in a 1:1 ratio using Clinsight® online randomization system. Patients will be stratified according to the type of PET-tracer used (choline, PSMA or FACBC) and the type of MDT (SBRT or sLND) (Fig. 1). As this is an open label trial, randomization will not be blinded.

**Fig. 1 Fig1:**
[figure not shown]
Trial design. **PCa** = prostate cancer, **MDT** = Metastasis-directed therapy, **sLND** = salvage lymph node dissection, **SBRT** = stereotactic body radiotherapy, **ADT** = androgen deprivation therapy, **WPRT** = whole pelvic radiotherapy, **RT** = radiotherapy

Patients will be randomized to receive one of the following treatments (Fig. 1):

**Arm A:**
sLND + 6 months of ADT orSBRT (30 Gy in 3 fractions) + 6 months of ADT

**Arm B:**
sLND + WPRT (45 Gy in 25 fractions) + 6 months of ADT orWPRT with simultaneous integrated boost (45 Gy in 25 fractions with SIB up to 65 Gy) + 6 months of ADT

### Evaluation during treatment

***Following sLND:***
Physical examination including Performance score at dischargePSA measurement at the first postoperative visit (4 weeks)Toxicity assessment using Clavien-Dindo scale at dischargeConcomitant medicationOperating characteristics: surgical technique, operating time, blood loss, number of nodes removed per lymph node region, number of positive nodes per lymph node region, indicate lymph node regions sampled.Nodes should be sent in separate containers for histopathological analysis.

***WPRT or SBRT:***
Physical examination at the end of treatmentAcute toxicity assessment (once a week for WPRT; for SBRT at the end of treatment): the highest grade of adverse events during radiotherapy will be reported at the end of treatment.Concomitant medicationTreatment planningRecord planning results

